#### Secondary Objective 6: Usability and Technology Acceptance

The audiotapes will be transcribed, and content analysis will be performed. The content analysis will be data driven. The data codes will be generated inductively by the collected data. Along with coding, a small number of themes or categories will be generated. The analyses will be performed by an RA, and agreement in the interpretations will be achieved through a discussion between the research team members. The validity of the interpretations will be discussed with and agreed upon by every member of the research team.

Quantitative analyses will be conducted using the SPSS version 27.0, and qualitative analyses will be conducted using NVivo10 (QSR International) software.

### Ethics and Dissemination

#### Research Ethics Approval

All procedures are approved by the ethics committee of Alberta University and the Northern Alberta Clinical Trials Research Centre, Canada.

#### Incentives

All participants will receive a coffee shop gift card after completing the study. The value of the coffee shop gift card will be CAD $25 (US $20.49).

### Withdrawal From the Study

The participants and substitute decision makers can request to withdraw from the study at any time, either verbally or in writing. The participants will be able to withdraw from the study at any time before the group analysis is calculated. If a participant withdraws, their information will not be taken into account for analysis. In the event that a participant requests to have their data destroyed, the research team will honor this request by shredding and recycling the paper records and erasing any records stored on a computer hard drive using commercial software apps designed to remove all data from storage devices. However, once all the participants’ data have been analyzed, a participant cannot withdraw. The participants will be informed of this in the consent letter. The deadline for withdrawal will be once all the participants’ data have been collected and the data analysis is underway. This will be around the 16th month of the study.

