### Outcome Variables

#### Primary Objective and Secondary Objectives 1 to 4: Primary Outcome Variables

The retention rates and intervention compliance will be calculated for the primary objective. The retention rates will be calculated according to the participants’ discontinuation of the interventions and their absence at the posttest at week 10. Intervention compliance means all of the hand rehabilitation sessions are completed by each group [21]. This study’s primary outcome variables for secondary objectives 1 to 4 are related to range of motion and strength: (1) AROM and PROM of wrist flexion and extension and forearm pronation and supination, (2) grip strength, and (3) pinch strength.

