### Data Analyses

#### Primary Objective and Secondary Objectives 1 to 4

Data analyses will be conducted using the intention-to-treat principle. Complete case analysis will be the primary method for dealing with missing data equal to or more than 10%. This is the most common method for dealing with missing data and reducing the risk of bias [27]. For missing data of less than 10%, we will use a simple imputation method by replacing the missing data with the average participants in the same strata (ie, medical condition). The analyses will focus on descriptive statistics and CI estimation rather than formal hypothesis testing [28]. Descriptive statistics will be used to characterize the groups at the pretest and posttest as well as during weeks 2, 4, and 8. The outcome variables as well as other data such as the length and dosage of each intervention will be summarized as n (%), mean (SD), or median (IQR), as appropriate. The retention rates, intervention compliance, and missing data will be summarized for outcomes related to the secondary objectives, which, together with the estimates, will assist in calculating the sample size for a definitive trial. As this study aims to assess the feasibility of conducting a definitive trial, clinical effectiveness is a secondary objective (ie, the study’s proof-of-concept element). In this regard, comparisons of the outcome variables at the pretest (week 0) and posttest (week 10) within the groups will be performed using a paired two-tailed *t* test (or a Wilcoxon signed-rank test if the data are not normally distributed) for AROM, PROM, grip strength, and pinch grip force and a Wilcoxon signed-rank test for the PRWE. Comparisons between the groups at the pretest and posttest will be performed using a *t* test (or a Mann-Whitney *U* test if the data are not normally distributed) for AROM, PROM, and grip strength and a Mann-Whitney *U* test for the PRWE. With our sample size, there would be a power of 0.8 to detect a medium effect size of Cohen *d*=0.25. However, we are aware that our study might be underpowered due to the sample size. If no statistically significant differences are found, our results will be classified as inconclusive rather than negative. We will report 95% CIs and interpret the level of uncertainty based on them [28]. In addition, we will explore the effects of the covariates using general linear models or multilevel mixed models when appropriate. All the α levels of significance will be set at *P*≤.05 (two-tailed).

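### The rule that drops all information of withdrawn participants contradicts intention-to-treat and conflicts with the definition of retention; read literally, it could also overstate retention

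*Protocol article*

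**What the plan says.** Four statements in the protocol article bear on this point.

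- **Withdrawal From the Study** sets the rule: "If a participant withdraws, their information will not be taken into account for analysis". On timing it says: "The participants will be able to withdraw from the study at any time before the group analysis is calculated". The section places that deadline at around the 16th month of the study. Destruction of records is a separate step: "In the event that a participant requests to have their data destroyed, the research team will honor this request".
- **Data Analyses** (primary objective and secondary objectives 1 to 4) says: "Data analyses will be conducted using the intention-to-treat principle". On missing values it says: "Complete case analysis will be the primary method for dealing with missing data equal to or more than 10" (per cent). Below that threshold, the mean of participants in the same stratum is imputed.
- **Outcome Variables** ties retention to the main aim: "The retention rates and intervention compliance will be calculated for the primary objective". Retention is worked out from participants' "discontinuation of the interventions and their absence at the posttest at week 10".
- **Data Analyses** also lists the summaries of retention, compliance and missing data, and says that with the estimates they will help in sizing the definitive trial.

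No passage exempts the retention, compliance or missing-data summaries from the withdrawal rule.

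**The concern.** Intention-to-treat means that everyone randomised is analysed in the arm to which they were allocated, as far as their data allow. A rule that removes a randomised participant's observed values because of something that happened after allocation is incompatible with it. The trial is open to participants and therapists, so the decision to withdraw may depend on the arm.

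The second issue is closer to the purpose of the study. Retention and compliance are the two outcomes named for the primary objective. If withdrawn people are left out of every analysis, and retention is one of the analyses, the people removed are ones whom retention is meant to count as lost. An overstated retention rate would then pass into the planning of the definitive trial as too small an allowance for dropout.

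**Working it through.** **Step 1: the texts side by side.** The withdrawal rule is unconditional and runs until the group analysis. It can therefore discard measurements from weeks 0, 2, 4 and 8, and even week 10, that were actually obtained. The complete-case rule does not reconcile this with intention-to-treat: complete-case handling concerns values that are missing, whereas the withdrawal rule sets aside values that were observed. Nor does the destruction clause explain the exclusion, since it covers only those who ask for destruction.

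**Step 2: inputs for the size.** The protocol gives no expected retention figure to reproduce. Its Sample Size section gives 94 participants (47 per group) and a 30% dropout allowance.

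- Losses: 0.30 × 94 = 28.2, taken as 28.
- Completers: 94 − 28 = 66.
- Share of the 28 losses that are formal withdrawals: not given. Assumption, varied from 0% to 100%.
- Further assumption: nobody who attends week 10 withdraws afterwards.

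The check does not depend on whether 94 is the right size for the stated power.

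**Step 3: formulas.** Let w be the number of formal withdrawals among the 28.

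- Retention with everyone randomised in the denominator = 66/94 = 70.2% (Wilson 95% CI 60.3% to 78.5%), whatever w is.
- Retention under the literal rule = 66/(94 − w).
- Dropout inflation factor implied for a later trial = (94 − w)/66.
- Apparent share missing at week 10 = (28 − w)/(94 − w).

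| Share of losses formally withdrawn | w | Retention under the literal rule | Inflation factor | Apparent missing at week 10 |
|---|---|---|---|---|
| 0% | 0 | 66/94 = 70.2% | 1.42 | 28/94 = 29.8% |
| 25% | 7 | 66/87 = 75.9% | 1.32 | 21/87 = 24.1% |
| 50% | 14 | 66/80 = 82.5% | 1.21 | 14/80 = 17.5% |
| 75% | 21 | 66/73 = 90.4% | 1.11 | 7/73 = 9.6% |
| 100% | 28 | 66/66 = 100% | 1.00 | 0/66 = 0% |

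At one half, the reported 82.5% already lies above the upper confidence limit of the full-denominator estimate (78.5%).

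**Step 4: a knock-on effect.** The missing-data method changes at 10%. With all 94 counted, 29.8% are missing and complete-case analysis applies. With w = 20 the apparent figure is 8/74 = 10.8%; with w = 21 it is 7/73 = 9.6%. So from 21 formal withdrawals on, a literal reading would also switch the method to mean imputation.

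**The case against.** The strongest reply is that retention has its own definition, and that definition counts discontinuation and absence at week 10. Someone who withdraws during treatment is such an event. The withdrawal section speaks of a participant's information and then of paper and computer records, so it may mean collected data only and not the fact of leaving. The protocol also commits to CONSORT guidance for feasibility trials. On that reading retention is not inflated. This stands: a reader might infer that the rule certainly inflates retention, and the document does not support that. It supports a conflict between two sections which, on one reading, leads to inflation.

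A second reply concerns selection at week 10. A reader might infer that the withdrawal rule is what leaves a selected sample for the between-group comparison. Mostly it is not. A person who leaves before week 10 has no posttest, and at 30% loss the complete-case rule removes that person from the week-10 comparison anyway. What the withdrawal rule adds is the loss of their baseline and interim data, the loss of week-10 data from anyone who withdraws after that visit, and the effect on the 10% threshold.

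Third, a promise not to use data differs from a promise to destroy it. The consent letter is not shown, so it cannot be concluded that participants were never promised non-use. This limits how a change can be applied to people already enrolled. It does not justify the rule for those still to be recruited.

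Finally, this is a feasibility trial that puts description and confidence intervals ahead of testing, and retention only assists in sizing the next trial. That lowers the stakes for the effect estimates, but not for retention, which belongs to the primary objective.

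**Conclusion.** The contradiction with intention-to-treat is in the current text and holds on any reading: observed data of randomised participants are discarded, without any request from them to destroy the data. The withdrawal section also conflicts with the definition of retention, and the two must be reconciled.

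The effect on the reported retention rate is conditional. If the withdrawal rule is applied literally to the feasibility summaries, a true 70.2% could be reported as anything from 70.2% to 100%, and the implied dropout inflation could fall from 1.42 to as low as 1.00. This rests on the plan's own 94 and 30%, on an unknown share of formal withdrawals, and on no withdrawals after week 10. The 100% end is a bound, not a forecast. If withdrawals are counted as disposition events, the effect on retention is nil and the discarding of observed data remains.

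**What to change.** Replace the sentence in Withdrawal From the Study with wording such as: *Data collected up to withdrawal are retained and analysed as randomised unless the participant asks for their removal or destruction. Every randomised participant stays in the participant flow and in the denominators of the retention, compliance and missing-data rates.*

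Align the consent text with this through an ethics amendment. The study was launched in April 2020, so some participants may already have consented under the present terms. For them, honour those terms for outcome data, and count them in flow and retention without identifying data.

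The cost is the protocol and consent amendment, with no extra data collection, and possibly a less favourable retention figure. The protocol describes the study as on hold, so the change is best made before recruitment resumes. It does not cure the loss of people without a week-10 measurement, which comes from the complete-case rule.

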### Consent or Assent

Signed consent will be obtained from all participants in the study. For those who are unable to give their informed consent, one of the therapist researchers (CH or DY) or another therapist involved in the recruitment process (JS or GD) will approach each potential participant and his or her substitute decision maker to provide information about the study. If these potential participants and their substitute decision makers give their consent, the substitute decision makers will sign the consent form, and we will seek the potential participants’ assent.

### Confidentiality

We will assign numerical codes to the participants instead of using their names or other identifiers. Only the study coordinator will have access to the master list where these codes are linked to the participants’ first names. With the exception of direct conversations with each participant, their names will not be used, only their numbers will be used. Hard copies of the consent forms, questionnaires, and study notes will be kept in a locked filing cabinet in a laboratory ([name]). All the deidentified electronic study documents will be encrypted and stored on a password-protected computer located in a laboratory ([name]).

### Access to Data

All the principal investigators will be given access to the cleaned data sets. The master list will be stored on a password-protected computer located in the principal investigator’s laboratory ([name]). Only the study coordinator will have access to this master list. The data will be retained for 5 years. There are no plans for future use of the data other than publishing them in peer-reviewed journals and at conferences. The data will not become part of a data repository and will not be involved in the creation of a research database or registry for future research use. After 5 years, the data will be destroyed. This will be done by shredding the paper records. Records stored on a computer hard drive will be erased using commercial software apps designed to remove all data from storage devices.

### Quality Assurance and Safety

We have established an advisory committee to monitor the progress of the study and, if necessary, to provide recommendations to the team members for discontinuation, modification, or continuation of the study. This committee will include our current partners, as follows: (1) Glenrose Rehabilitation Hospital, (2) Royal Alexandra Hospital, (3) experts in the areas of economics and commercialization and experts in health technology assessment, (4) patient representatives who have undergone hand therapy, and (5) certified hand therapists.

We will follow the CONSORT guidelines for clinical trial feasibility [17]. In addition, we will assess the quality of our study using the PEDro (Physiotherapy Evidence Database) scale [24].

## Results

The FEPSim study was launched in April 2020. Currently, this study is on hold because of the global COVID-19 pandemic. The recruitment process is expected to resume by September 2020, and the primary impact analysis is expected to be conducted by December 2020.

The results of this project will inform the development of best practices for clients with clinical conditions of the forearm, wrist, and hand, which impact the health of more than 35,072 Albertans annually. Improved rehabilitation can decrease the time needed to achieve functional outcomes, thereby decreasing health care costs. Returning patients more quickly to their valued occupations, including work, can decrease the costs associated with home care and other social services and reduce injury-related work time loss. FEPSim takes up little space, is much less expensive than comparable devices, and can easily be implemented throughout the public and private sectors in Alberta’s health system. This project is an excellent example of how industries and the health care system can support each other to grow and diversify Alberta’s economy and promote the entry of this valuable technology into the global rehabilitation market.

## Discussion

The primary objective of this study is to assess the feasibility of conducting a definitive trial on the effectiveness and cost-effectiveness of the FEPSim device for individuals with medical conditions that affect hand function. The level of evidence for the rehabilitation of hand function due to MSDs and neurological injuries and diseases is conflicting and differs according to the medical condition as well as the strategies or modalities implemented and the equipment and materials used during the sessions. The equipment that is currently available for hand therapy is either low cost or does not allow therapists to grade their therapeutic activities and exercises accurately, or it consists of high-tech devices that many clinicians or health care systems cannot afford. FEPSim has the potential to become a sound alternative in the midpoint between these 2 extremes. FEPSim has a technological readiness level of 7 [11]; thus, it has a sufficient level of readiness that can be tested in a real-world clinical setting. This feasibility study is the first RCT to evaluate the potential benefits of the FEPSim, not only in terms of functional outcome variables but also in terms of the costs associated with the delivery of hand rehabilitation in 2 large hospitals. Conducting this RCT will provide valuable information. First, the estimates can be used for sample size calculations in future RCTs. Second, as we will measure the patients’ outcome variables on 4 different occasions during the intervention, the results of this study will guide therapists by providing the expected percentage of a patient’s improvement and data on how the progress is made over a period of 10 weeks. The literature suggests that early hand therapy has an effect on range of motion and strength [12]; thus, this study will provide information about FEPSim’s potential to speed up the patient recovery process and reduce the length of treatment, which in turn may reduce treatment costs. In addition, the findings of this project can be used by therapists to develop exercise or activity standard protocols for hand rehabilitation interventions using the FEPSim device. Third, the estimations of the resource use and associated costs of the interventions during each arm of the trial will inform individuals who are responsible for purchasing or procurement decisions and who work with hospital budgets. The results of this project will provide them with information about the feasibility of adopting FEPSim.

In conclusion, this study will provide valuable information, such as the measurement of comparative intervention effects, technology acceptance by hand therapists, the associated costs of treatment, and product costs. This will contribute to the evidence planning process, which will be crucial for the future adoption of FEPSim.

## Abbreviations

AICE: Accelerating Innovation Into Care
AROM: active range of motion
BTE: Baltimore Therapeutic Equipment
CONSORT: Consolidated Standards of Reporting Trials
MSD: musculoskeletal disorder
PEDro: Physiotherapy Evidence Database
PROM: passive range of motion
PRWE: patient-rated wrist evaluation
RA: research assistant
RCT: randomized controlled trial
